
#### Blood tests

All blood tests are conducted in accordance with the department’s standard procedures.
Total testosterone (nmol/L), luteinizing hormone (IU/L), follicle-stimulating hormone, (IU/L), and sex hormone-binding globulin (nmol/L).Lipid profile (total cholesterol, high-density lipoprotein cholesterol, low-density lipoprotein cholesterol, triglyceride) (mmol/L).C-reactive protein (mg/L).

#### Safety parameters

The following values are assessed: hemoglobin, hematocrit, creatinine, carbamide, sodium (Na^+^), potassium (K^+^), calcium, international normalized ratio (INR), liver tests, PSA, and glucose.

For the following parameters, safety thresholds are defined: hematocrit (safety threshold, values > 0.50), liver tests (albumin, alanine aminotransferase, γ-glutamyltransferase, bilirubin) (safety threshold, liver test values > 3 times the upper limit of normal), and PSA (safety threshold, increase to > 50%).

Other safety parameters are blood pressure (assessed using a digital blood pressure monitor, measured in mmHg) and facial hirsutism (assessed using the two face-related items of the modified Ferriman-Galwey hirsutism score, 0–8 points) [56], hoarseness (assessed through weekly interviews and hospital controls every 3 weeks), edema (assessed through weekly interviews and hospital controls every 3 weeks), and falls (a question regarding falls will be part of an interview guide used for the weekly telephone calls). Other AEs/adverse reactions (ARs) will be assessed through weekly interviews and hospital controls every 3 weeks.

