### Recruitment

Patients admitted to the Hip Fracture Unit at the Orthopedic Department of Copenhagen University Hospital Hvidovre will be screened for eligibility (see inclusion and exclusion criteria in Table 1). The sampling method is consecutive, though screening and inclusion will be discontinued during trial staff’s absence. A screening log will be kept. Annually, approximately 475 patients above 60 years of age are operated at the Hip Fracture Unit. We assume that 20% would be excluded due to nursing home residency, another 20% would be excluded due to cognitive impairments, and the remaining criteria would account for approximately 25% exclusions. That would leave us with 14 eligible patients per month. We aimed at completion of recruitment within 1 year, but because recruitment has been lower than expected, the recruitment period has been extended to September 2020.

**Table 1 Tab1:** Inclusion/exclusion criteria

*Inclusion criteria*	
• Patients who have undergone surgery for a hip fracture at Amager-Hvidovre University Hospital and admitted to the Hip Fracture Unit at the hospital	
• Age ≥ 60 years	
• Ability to speak and understand Danish and having a Danish Social Security number	
• Able to give written informed consent	
• Residing at home and with an independent prefracture indoor walking ability (New Mobility Score ≥ 2)	
*Exclusion criteria*	
• Postoperative weight-bearing restrictions	
• Multiple fractures	
• Active cancer or suspected pathological fracture	
• Patient unable/unwilling to cooperate for testing and rehabilitation	
• Planned/elective hospitalization within the trial period	
• Cognitive dysfunction determined by chart review, reported by nursing staff, or observed by trained research staff (disoriented, dementia, active delirium)	
• Uncontrolled blood pressure (systolic > 150 mmHg or diastolic > 100 mmHg)	
• Heart disease in the form of peri-, myo-, or endocarditis	
• History of stroke with motor disability	
• Heart failure (New York Heart Association class III and IV)	
• Evidence of kidney failure or renal impairment (estimated glomerular filtration rate < 30 ml/min/1.73 m^2^ or serum creatinine > 200 μmol/L)	
• Abnormal liver function tests (alanine aminotransferase, γ-glutamyltransferase, bilirubin, or alkaline phosphatase > 2 times the upper limit of normal) or history of hepatic tumor	
• Elevated hematocrit ≥ 50%	
• History of breast or prostate cancer	

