### Criteria for discontinuation

Safety parameters are listed under the “Secondary outcomes” heading and will be observed throughout the study. If values of hematocrit, liver tests, and prostate-specific antigen (PSA) exceed the safety thresholds, the treatment with Deca-Durabolin will be discontinued. Further, if women experience androgenic side effects, treatment will be discontinued. Regarding the remaining safety parameters, where no safety threshold is specified, values outside the reference interval will be evaluated by the medical doctors trained in the protocol and relevant action will be taken if necessary.

In accordance with the Declaration of Helsinki, patients have the right to withdraw from the trial at any time for any reason. Further, the investigator has the right to withdraw a patient from the trial at any time if a withdrawal is considered in the best interest of the patient.

Patients who have ceased intervention prior to its determination will be asked to follow the scheduled controls, and data will be collected according to the protocol. Patients who choose to withdraw from the trial will be asked the reason why. However, it is emphasized that the patient is not obliged to state the cause. If a patient drops out and is unwilling to follow the protocol, permission will be asked to continue weekly phone calls to monitor potential side effects (for 4 weeks after last injection). Further, the patient will follow standard treatment for hip fracture and see the orthopedic surgeon at the regular postoperative visit.

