### Statistical analyses

Descriptive statistics will be used for presenting baseline characteristics. Continuous data will be examined for normality of distribution using Q-Q plots. Data will be presented as mean (SD) when normally distributed, otherwise as medians (q1–q3) or as frequencies with percentages.

The statistical analysis of the primary outcome will be two-sample *t* test or Wilcoxon rank-sum test as appropriate to determine systematical differences in change scores between the intervention and control groups. For the secondary outcomes, tests will be performed using either chi-square or Fisher’s exact test for categorical data or two-sample *t* test or Wilcoxon rank-sum test for continuous data. Analysis of safety parameters and feasibility endpoints will be descriptive. The level of significance will be set at *P* < 0.05, and confidence intervals (CIs) will be displayed at 95% CI around differences.

The analysis will follow the intention-to-treat principle and include all randomized patients. To create a full analysis set, missing data will be imputed using a multiple imputation technique. Secondary analysis will be conducted for both primary and secondary outcomes on the per-protocol data, where patients are excluded if they are not compliant with the trial. Compliance in relation to per-protocol analysis is defined as 75% intake of nutritional supplement, 75% completed training sessions, and 100% received injections. No interim analyses will be conducted.

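### The liver stopping rule applies a limit of more than 3 times the upper limit of normal to albumin, which can never reach it

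*Protocol article*

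**What the plan says.** Three places in the protocol article bear on this point.

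- **Safety parameters** defines thresholds for hematocrit, liver tests and PSA. The liver entry reads "liver tests (albumin, alanine aminotransferase, γ-glutamyltransferase, bilirubin) (safety threshold, liver test values > 3 times the upper limit of normal". A single upward limit covers all four named tests.
- **Criteria for discontinuation** makes the thresholds binding: "If values of hematocrit, liver tests, and prostate-specific antigen (PSA) exceed the safety thresholds, the treatment with Deca-Durabolin will be discontinued". For the other safety parameters, "where no safety threshold is specified, values outside the reference interval will be evaluated by the medical doctors trained in the protocol". The same section adds that "the investigator has the right to withdraw a patient from the trial at any time", if this is judged to be in the patient's best interest.
- **Table 1 (Recruitment)** uses a similar list of four tests to exclude patients at entry, with a different fourth test and a lower multiple: "alanine aminotransferase, γ-glutamyltransferase, bilirubin, or alkaline phosphatase > 2 times the upper limit of normal".

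INR is also measured ("international normalized ratio (INR), liver tests, PSA, and glucose") and has no threshold of its own. Under Statistical analyses, "Analysis of safety parameters and feasibility endpoints will be descriptive".

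**The concern.** Alanine aminotransferase, γ-glutamyltransferase and bilirubin rise when the liver is injured, so a multiple of the upper limit is a workable stopping limit for them. Albumin behaves differently. It cannot rise to a multiple of its upper limit, and impaired liver function lowers it. Including it under a limit of more than 3 times the upper limit creates a stopping criterion that is written down but cannot act.

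There is a secondary effect on a literal reading. The physician review covers only parameters without a specified threshold. Albumin nominally has one, so a low albumin falls outside that review, while the threshold that displaces the review is never met.

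This matters because preliminary safety is part of the first hypothesis (Purpose), and the liver rule is one of only three laboratory stopping rules. The pilot is also meant to be the basis for a larger confirmatory trial, into which the wording could be carried.

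**Working it through.** The threshold is a stated multiple, so there is no calculated figure in the plan to reproduce. The check asks whether albumin could ever cross it.

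**Inputs**
- Multiple: 3 (Safety parameters).
- Albumin upper limit of normal: not given in the article. Assumed range 40 to 55 g/L.
- Illustrative low albumin: 20 g/L (assumed).

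**Step 1. Where the trigger lies, and where a low value sits**

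Trigger = 3 × upper limit. Ratio of a low albumin to the upper limit = 20 ÷ upper limit.

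| Assumed upper limit (g/L) | Trigger (g/L) | 20 g/L as a multiple of the upper limit |
|---|---|---|
| 40 | 3 × 40 = 120 | 20/40 = 0.50 |
| 45 | 3 × 45 = 135 | 20/45 = 0.44 |
| 50 | 3 × 50 = 150 | 20/50 = 0.40 |
| 55 | 3 × 55 = 165 | 20/55 = 0.36 |

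No trigger in the range is attainable. A markedly low albumin has a ratio of 0.36 to 0.50 against a required ratio above 3, so deterioration moves the value away from the trigger. The result does not depend on which upper limit is chosen.

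**Step 2. The two liver lists side by side**

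| Test | Entry, Table 1 (> 2 times) | On treatment, Safety parameters (> 3 times) |
|---|---|---|
| Alanine aminotransferase | yes | yes |
| γ-Glutamyltransferase | yes | yes |
| Bilirubin | yes | yes |
| Alkaline phosphatase | yes | no |
| Albumin | no | yes |

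Three of the four tests are shared. Albumin stands where alkaline phosphatase stands at entry. Working limbs in the stopping rule: 4 − 1 = 3.

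**Step 3. Does any reading of the text rescue it?**
- If albumin was intended, its threshold is void.
- If albumin was written for alkaline phosphatase, the bracket names the wrong test, and alkaline phosphatase is an entry criterion with no stated on-treatment limit.
- If alkaline phosphatase was left out on purpose, the limit still cannot apply to albumin.

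Each reading needs a correction.

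**The case against.** The strongest reply is that this is a drafting slip with no demonstrated effect on conduct. An out-of-place test in the bracket neither stops a patient wrongly nor disables a limb that works. Three liver markers still stop treatment, INR outside its reference interval goes to a physician, and the investigator may withdraw any patient. All of this stands, and it is why the point is minor.

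Second, Data monitoring says that out-of-range laboratory results are recorded as adverse events if they lead to clinical action, which presupposes that someone may act on a low albumin. That is fair as far as it goes, but the provision governs recording. It does not direct anyone to review albumin.

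Third, the gap in physician review is not peculiar to albumin. Read literally, the same wording leaves out any test with a threshold while it is below that threshold, for example alanine aminotransferase at 2.5 times the upper limit. This is correct, and the gap should not add to the weight of the point. Albumin differs only in that no value ever reaches its threshold.

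Fourth, the article condenses a full protocol that is not shown, and the rule the trial physicians use may be right. That limits the finding to the printed wording.

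**Conclusion.** The point holds, as a minor one. One of the four named limbs of the liver stopping rule cannot trigger at any albumin value and points in the wrong direction; the other three work. The conclusion rests on an assumed albumin upper limit, but any value from 40 to 55 g/L gives the same answer.

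The difference from Table 1 suggests a slip for alkaline phosphatase. This is an inference that the article neither confirms nor excludes. The number of patients who might be affected cannot be estimated from the document. The primary outcome, the sample size and the between-group tests are unaffected. Confidence is high for the wording as printed; nothing is claimed about the unseen full protocol.

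**What to change.** First establish which test was intended. Then:

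- **If albumin is to be monitored:** limit the bracket under Safety parameters to alanine aminotransferase, γ-glutamyltransferase and bilirubin, keep the limit of more than 3 times the upper limit of normal for those three, and list albumin among the parameters without a threshold. Albumin outside its reference interval then goes to the existing physician review, as INR already does.
- **If alkaline phosphatase was meant:** substitute it for albumin in the bracket. The on-treatment list then matches the tests used at entry.
- **If the full protocol is already correct:** correct only the article.

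The cost is one sentence of wording, with no extra patients or visits. The downside is some additional physician reviews of low albumin or, if alkaline phosphatase is substituted, possibly a few more treatment stops from a fourth working marker.

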#### Feasibility outcomes

Feasibility will be assed according to the following aspects: number of eligible patients, inclusion rate per month, feasibility and suitability of outcome measures, acceptability of the treatments to the patients, adherence to the treatment, retention to the scheduled controls and follow-up, and number and severity of AEs.

### Sample size

The sample size is determined on the basis of the primary outcome (change in knee-extension strength of the fractured limb) and calculated to detect a between-group difference in the change score of 0.2 N∙m/kg in favor of the intervention group using Lehr’s formula with an SD of 0.22 N∙m/kg. The difference in change scores of 0.2 N∙m/kg is defined by the authors, and it is a larger difference than what could be considered the minimal clinically important difference. Because we only wish to explore the potential of effect in this pilot trial [57], and not establish effect, we argue that it is acceptable. The SD of 0.22 N∙m/kg is obtained from a previous study [3]. Hence, we acknowledge that if this trial shows feasibility and preliminary effect of the intervention, confirmatory effect will need to be demonstrated in at least one phase III-like confirmatory trial. On the basis of this estimate, 20 patients are needed in each group using a standard of 80% power and type I error rate of 5%. Forty-eight patients are therefore planned for inclusion in the present trial to allow for an expected dropout rate of 20%. In case of dropout, new patients will be enrolled in the trial to ensure a minimum of 20 patients in each group who have completed the intervention.

### Randomization and allocation

The patients will be randomly assigned to one of the two groups by a 1:1 allocation ratio. Block randomization (blocks of 2 and 4) will be used, and patients will be stratified for type of fracture (cervical femoral versus trochanteric hip fracture) and sex. The allocation sequence is computer-generated (random number generator) by a qualified person not involved in the trial. The allocation sequence is retained in a locked cabinet by the person generating the sequence. To ensure allocation sequence concealment, sequentially numbered, opaque, sealed envelopes are used. When a person is included in the trial, the coded envelope is broken by the nurse injecting the trial medication. The envelopes contain information on allocation and a registration form used for medicine accounting. The envelopes will be retained by the nurse injecting the medication and kept in the nurse’s office, which is geographically separated from the hip fracture unit and the Department of Physiotherapy.

Information about allocation will not be revealed before all data analysis has been performed.

### Blinding procedure

The patients, healthcare providers, intervention deliverers, data collectors, and outcome assessors are all blinded to whether the patient has received trial medication or placebo. The only person not blinded is the nurse drawing the envelope and injecting the medication/placebo, but she has no other involvement in the trial. The nurse is instructed not to reveal to the patients to which intervention they are allocated. No effort will be made to blind the research hypotheses from the participants.

Blinding for the individual patient will be broken only in cases where the continued treatment of the patient requires knowledge of allocation. Twenty-four-hour access to unblinding is assured. If the code is broken, date and reason will be registered, and the envelope will be signed by the investigator.

### Data collection and management

For each patient included in the trial, an electronic case report form (CRF) will be completed in a browser-based database, Research Electronic Data Capture (REDCap). Data entered via REDCap will be stored via an encrypted connection and will meet the applicable requirements for data security. The REDCap option of validating the entered data will be used to promote the quality of data. Correction of data will be visible and accessible through REDCap’s audit trail. The audit trail will be saved equivalent to trial data. The trial data will be saved for at least 5 years as required by the Danish Data Protection Agency (journal no. AHH-2017-090, I-Suite no. 05980). The principal investigator and sponsor are responsible for managing and archiving data in accordance with the relevant legislation, including the Act on Processing of Personal Data and Health Act.

### Data monitoring

The trial will be conducted in accordance with the International Council for Harmonisation of Technical Requirements for Pharmaceuticals for Human Use (ICH) principles of good clinical practice (GCP). The project is registered with EudraCT (identifier 2017-001543-13) and is monitored by the independent GCP unit at Copenhagen University Hospital Bispebjerg. The GCP unit will monitor the project throughout the trial and assure that the trial is executed, registered, and reported according to the protocol, written standard operating procedures, GCP, and Danish legislation. Scheduled monitoring visits will be conducted throughout the trial. The first initiating visit is prior to commencement of the trial. The focus of the following visit is on monitoring the trial master file, protocol compliance, data quality, and informed consent. Further, selected trial data are monitored (e.g., inclusion, dropout, completion, primary outcome, trial medication, randomization, allocation, drug compliance, medicine accounting, AEs). No additional auditing is planned.

AEs and ARs related to the trial will be recorded in the CRF throughout the trial period, starting from the day of the first injection and ending at week 16. The relationship (causality) between the AE and the trial medication and severity will be assessed by the principal investigator or any one of the medical doctors trained in the protocol. The summary of product characteristics for Deca-Durabolin is used as a reference when assessing if a serious AR is unexpected or expected.

It should be noted that the following conditions are considered to occur often after hip fracture surgery and can lead to prolonged hospitalization: nausea, vomiting, dizziness, postoperative urine retention due to catheterization, pain or irritation in relation to the bladder due to catheterization, diarrhea, pneumonia and cardiopulmonary influence, hemoglobin (Hb) < 9.7 g/dl and consequently blood transfusion, and divergent blood tests due to surgery. These will not be registered as AEs during hospital admission. Expected pain from the operation site will not be registered as an AE during the trial period. Further, edema of the fractured limb is common in the postoperative period, and especially for patients with trochanteric fractures compared with those with cervical femoral fractures [4], and will not be reported as an AE. Laboratory test results beyond the reference interval will be recorded as an AE only if they cause a clinical action.

All AEs/ARs will be followed until stabilization by either the relevant hospital department or the patient’s general practitioner.

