#### Trial medication

Nandrolone is a synthetic anabolic-androgenic steroid; it is protein-building, promotes mineralization of bones, and stimulates the formation of red blood cells. Nandrolone is structurally related to naturally occurring testosterone, but it shows enhanced anabolic effect and a reduced androgenic effect. Nandrolone is used medically in the form of esters (nandrolone decanoate) and is intended for use in osteoporosis in postmenopausal women and for some types of anemia. Deca-Durabolin is an intramuscularly administered depot preparation of nandrolone decanoate.
*Active arm (INT)*: Patients will receive intramuscular injections of nandrolone decanoate (Deca-Durabolin 50 mg/ml; Aspen, Durban, South Africa) every 3 weeks. The first injection will be administered at baseline and the last injection at week 12. The solution is injected into the gluteal muscle or rectus femoris. The dosage varies, dependent on gender and testosterone level (men). Women will receive 50 mg, men with total testosterone ≥ 11 nmol/L will receive 100 mg, and men with total testosterone < 11 nmol/L will receive a dose of 200 mg. The cut of 11 nmol/L for total testosterone is determined on the basis of the age-related reference interval (men 50–70 years, 8.4–25.4 nmol/L) and lies below the mean value of 14.6 nmol/L (24).*Placebo arm (CON)*: Patients will receive a placebo injection of 1 ml of sodium chloride 9 mg/ml (produced by Fresenius Kabi, Bad Homburg, Germany), following the same intervals as for the active agent. The fluid is injected intramuscularly, and the product has no therapeutic effect.

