#### General trial treatment procedures

Patients included in the trial will be treated according to the department’s standard procedures for surgery, anesthesia, and perioperative care. Type of operation is determined by a well-defined algorithm based on the type of fracture [32]. Standard perioperative care includes D vitamin and calcium supplementation dependent on the patient’s individual level. Further, a standardized liberal transfusion protocol is used with transfusion if hemoglobin (Hb) is < 9.7 g/dl.

After enrollment, patients will be assessed in regard to the study’s primary and secondary outcomes. Thereafter patients are randomized, and the first injection of the trial solution is administered by the dedicated nurse. In case of the primary nurse being absent, a second nurse trained in the protocol will substitute for her.

After discharge, the patient will receive weekly telephone calls from the project coordinator in order to ensure and monitor compliance. The patient will be asked about the amount of consumed nutritional supplement and attendance at physiotherapy sessions. Further, the patient will be asked about their well-being in order to detect potential side effects of the intervention. An interview guide will be used to assure systematic collection of information.

Every 3 weeks, the patient will attend a control visit at the hospital. The dedicated nurse will carry out blood tests and inject the treatment solution according to randomization group. Compliance with the trial as well as outcome/safety parameters will be monitored. Further, the nutritional supplement covering the following 3 weeks will be handed out at the visit.

The intervention period for the nutritional supplementation and exercise intervention is 12 weeks. The patient will receive the last injection at week 12. Further, at the 12-week appointment, an activity monitor will be applied to the patient’s thigh (activPAL; PAL Technologies, Glasgow, UK), which will monitor activity the following week.

Follow-up will occur during week 14, when patients will be assessed according to the primary and secondary outcomes. To ensure that all potential side effects are detected, one last telephone call is conducted during week 16, and thereafter the patient will have no further obligations in relation to the trial. See Fig. 1 for the flow of enrollment and trial-related events.

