**Fig. 2 Fig2:**
[figure not shown]
Schedule for enrollment, intervention, and outcome assessments (SPIRIT)

The baseline assessment might extend over 2 days in order to avoid patient exhaustion, and it will be conducted during the time period from postoperative day 3 until postoperative day 10. The follow-up assessment is conducted during week 14 from time of randomization (± 7 days from time of randomization). The control every 3 weeks is conducted within 3, 6, 9, and 12 weeks (± 7 days from time of randomization).

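### Adverse-event recording ends at a fixed week 16, so completers whose last injection comes late in its ±7-day window are followed for less than the 4 weeks used for dropouts

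*Protocol article*

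**What the plan says.** Four places in the protocol article bear on this.

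- **Timing of the last dose.** Trial medication: "The first injection will be administered at baseline and the last injection at week 12". Under General trial treatment procedures, injections are given at the three-weekly control visits: "The dedicated nurse will carry out blood tests and inject the treatment solution according to randomization group".
- **Visit window.** Outcome section, in the text below Fig. 2: "The control every 3 weeks is conducted within 3, 6, 9, and 12 weeks (± 7 days from time of randomization").
- **End of safety recording.** Data monitoring has adverse events and reactions recorded "starting from the day of the first injection and ending at week 16". General trial treatment procedures gives the last contact and its purpose: "To ensure that all potential side effects are detected, one last telephone call is conducted during week 16". Once that call has been made, the patient's part in the study is over.
- **Patients who drop out.** Criteria for discontinuation: "permission will be asked to continue weekly phone calls to monitor potential side effects (for 4 weeks after last injection").

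No section ties the end of recording to the actual date of the last injection for patients who complete treatment, and no window is given for the week-16 call.

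**The concern.** The article uses two clocks for the same purpose. For a patient who drops out, side-effect follow-up counts from the last injection. For a patient who completes all five injections, it stops at a study week, whenever the last injection was given. The clocks coincide only if the week-12 visit takes place on its nominal day. If that visit is late, the end of recording does not move with it, and a reaction that first appears after week 16 falls outside the recording period.

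What is at stake is the completeness of adverse-event capture. The first hypothesis (Purpose) includes preliminary safety, and the number and severity of adverse events is a listed feasibility outcome. The product is described as a depot preparation, so time since the last dose is a natural clock for side effects. An event that was never recorded cannot be recovered at the analysis stage.

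**Working it through.** All times are in days from randomization. The article does not write out the origin of week 16. Randomization, close to the first injection, is inferred from the Outcome and Data monitoring sections.

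**Inputs**
- Last injection: week 12 = 12 × 7 = day 84 (Trial medication).
- Window on that visit: 84 ± 7 = days 77 to 91 (Outcome).
- End of recording and last call: week 16 = 16 × 7 = day 112 (Data monitoring; General trial treatment procedures).
- Side-effect follow-up for dropouts: 4 × 7 = 28 days after the last injection (Criteria for discontinuation).

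**Nominal schedule.** 112 − 84 = 28 days = 4 weeks. This reproduces the dropout figure, so the article is consistent when visits occur on their nominal day.

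**Across the visit window**, follow-up = 112 − day of last injection:

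| Last injection | Recording after it | Against 28 days |
|---|---|---|
| Day 77 | 112 − 77 = 35 days | +7 |
| Day 84 | 112 − 84 = 28 days | 0 |
| Day 85 | 112 − 85 = 27 days | −1 |
| Day 91 | 112 − 91 = 21 days | −7 |

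Twenty-eight days after a day-91 injection is day 119, so an event first appearing on days 113 to 119 would not be recorded for that patient.

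**Sensitivity to the meaning of week 16**, for a day-91 injection:
- Sixteenth week, days 106 to 112: 106 − 91 = 15 to 112 − 91 = 21 days.
- Week following 16 completed weeks, days 112 to 118: 112 − 91 = 21 to 118 − 91 = 27 days.
- A +7-day tolerance on the call, which is not stated: 119 − 91 = 28 days.

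The latest permitted injection therefore gets less than 28 days on every reading except the one that adds an unstated tolerance. That every injection after day 84 falls short is specific to day 112. If recording ran to day 118, injections up to day 90 would still reach 28 days (118 − 90 = 28).

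**The case against.** The strongest reply is that nothing here is contradictory. Week 12 to week 16 is 4 weeks, as for dropouts, and the gap appears only when a visit tolerance is combined with a hard stop at day 112 that the article does not spell out. A tolerance for one telephone call is a detail that an article may leave to the full protocol. This stands in part: a reader might infer an outright contradiction, and the nominal schedule does not support that. But the article does state the visit window, the end of recording and the 4-week period, and together these leave late-injected patients short unless a further tolerance is assumed.

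Second, the 4 weeks is written only for patients who leave the trial, by telephone and with their permission. A reader might take it as the plan's safety standard for the depot product. The article neither says so nor justifies the figure by the formulation. It serves here only as the article's own comparator, matched by its nominal schedule for completers.

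Third, a reader might infer that completers are monitored less well than dropouts overall. That is not supported. Completers have a safety assessment at week 14, nominally day 98 and so 7 days after even a day-91 injection, as well as the week-16 call. Those injected before day 84 have more than 28 days. Only the count of days can be shorter, and only after a late visit. Following events until they stabilize does not close the gap, because it concerns events already recorded.

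Fourth, a fixed end gives every completer the same total recording period from the first injection, and anchoring to the last injection gives that up. This is a real but small cost.

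**Conclusion.** The point holds as a minor one. With week 16 taken as day 112 and no tolerance on the call, completers injected on days 85 to 91 have 27 to 21 days of recording after their last injection, against the 28 days used for dropouts. The largest shortfall on that reading is 7 of 28 days. Under the other readings of week 16 without an added tolerance, a day-91 injection gets between 15 and 27 days. For these patients the aim set for the last call, detecting all potential side effects, is not fully met.

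The number of patients affected cannot be given, because the article says nothing about how visits spread over the window. A reader might assume an even spread and conclude that about half of completers fall short, but nothing in the document supports that assumption. Nor should the point be read as bias between arms. The schedule is the same in both, allocation is randomized and blinded, and the safety analysis is descriptive. The primary outcome, its test and the sample size are unaffected.

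**What to change.** Reconcile General trial treatment procedures and Data monitoring with Criteria for discontinuation and the visit windows under Outcome. The end of adverse-event recording and the existing last call should be stated relative to the patient's actual last injection, in terms that are consistent for completers and dropouts, with any tolerance on the call written out. The length of follow-up is for the trial team to decide and is not proposed here.

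The cost is about one sentence in each of the two sections. To gauge the effect only: if the article's existing 28 days were the common figure, recording would end on day 105, 112 or 119 for a last injection on day 77, 84 or 91. The existing call would move by up to about a week for some patients and the total recording period would vary slightly between patients. No extra visit or procedure is needed.
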